### Interventions

2.6

Experimental Group: Participants will receive SQFWG, composed of *Astragalus membranaceus* (Huangqi), *Codonopsis pilosula* (Dangshen), *Atractylodes macrocephala* (Baizhu), *Gallus domesticus* (Jineijin, endothelium corneum of chicken gizzard), stir-fried *Hordeum vulgare* (Chao Maiya), stir-fried *Setaria italica* (Chao Guya), *Glycyrrhiza uralensis* (Gancao), and other herbs in specified ratios, in addition to the perioperative therapy. The granules will be administered orally at a dose of one packet three times daily, dissolved in hot water and taken after meals. Each treatment cycle is 3 weeks, synchronized with the chemotherapy schedule. Administration will continue concurrently with perioperative therapy until disease progression, unacceptable toxicity, or completion of the prescribed therapy. For patients undergoing surgery, oral administration will resume postoperatively based on recovery status.Control Group: Participants will receive a matched placebo in addition to the perioperative therapy. The placebo is designed to be indistinguishable from the active granules in outer packaging, dosage form (color, shape), and taste. Its composition includes: SQFWG extract powder (5%, sub-therapeutic dose), maltodextrin, a bitter flavoring agent, sucralose, yellow dextrin, and brown dextrin. Maltodextrin and sucralose conform to the standards for pharmaceutical excipients as per the Chinese Pharmacopoeia (2025 Edition, Volume IV). The bitter flavoring agent, yellow dextrin, and brown dextrin are food-grade additives compliant with national food safety standards. The dosing regimen (dose, frequency, and route) is identical to that of the experimental group.Perioperative Therapy (Both Groups): Participating centers will follow unified protocol-specified perioperative treatment principles based on contemporary CSCO and international guidelines. Based on the results of the KEYNOTE-585 (11) and RESOLVE (7) trials, the primary chemotherapy regimens are limited to SOX or XELOX. The preoperative phase will consist of 2–4 cycles of neoadjuvant SOX or XELOX chemotherapy, with or without immunotherapy. Postoperatively, participants will receive 4–6 cycles of adjuvant SOX chemotherapy (which may be followed by S-1 monotherapy) or 4–6 cycles of XELOX chemotherapy, with or without immunotherapy. Treatment will continue until disease progression, unacceptable toxicity, or completion of the planned cycles. The specific immunotherapy regimen is not restricted by the protocol. Immunotherapy (e.g., pembrolizumab, durvalumab, camrelizumab, or other PD-1/PD-L1 inhibitors) is permitted only for patients with biomarker evidence of potential benefit (e.g., PD-L1 CPS ≥5, MSI-H, or EBV positivity) based on current guidelines. The choice of agent is at the investigator’s discretion, the specific agent, number of cycles, and timing must be documented, but not restricted to reflect real-world practice.① Chemotherapy regimens:SOX regimen (3-week cycle): Oxaliplatin 130 mg/m², administered intravenously over 2 hours on Day 1; S-1 40–60 mg (based on body surface area: <1.25 m²: 40 mg; 1.25–1.5 m²: 50 mg; >1.5 m²: 60 mg), taken orally twice daily after meals on Days 1–14, followed by a 7-day treatment-free interval.XELOX regimen (3-week cycle): Oxaliplatin 130 mg/m², administered intravenously over 2 hours on Day 1; Capecitabine 1,000 mg/m², taken orally twice daily on Days 1–14, followed by a 7-day treatment-free interval.② Immunotherapy regimens:Pembrolizumab: 200 mg administered intravenously over 30 minutes on Day 1 of each 3-week cycle.Durvalumab: 1,500 mg administered intravenously over 60 minutes on Day 1 of each 4-week cycle.Camrelizumab or Sintilimab: Administered per standard institutional protocols at approved doses (typically 200 mg Q3W for Camrelizumab; 200 mg Q3W for Sintilimab).The protocol specifies the recommended dosing schedules for commonly used PD-1/PD-L1 inhibitors administered according to the approved product labeling and current clinical guidelines. The duration of immunotherapy is also defined in accordance with routine perioperative treatment recommendations.③ Dose adjustment rules:Dose modifications for chemotherapy are based on the severity of adverse events per NCI-CTCAE v5.0, including hematologic toxicity, thrombocytopenia, peripheral neuropathy, hepatic dysfunction, renal impairment, and other significant adverse events. For oxaliplatin-related neurotoxicity (grade ≥2), oxaliplatin may be held or reduced by 25%; for grade ≥3, oxaliplatin is discontinued. For thrombocytopenia (platelet <75×10^9^/L), oxaliplatin is held until recovery to ≥100×10^9^/L; for grade 3–4 thrombocytopenia, the dose is reduced by 25% upon re-administration. For S-1 or capecitabine, dose adjustments are based on gastrointestinal toxicity, hand-foot syndrome, and myelosuppression, using standard dose reduction levels (100% → 75% → 50% → discontinuation).Immunotherapy dose modifications follow current international consensus guidelines and the prescribing information for each immune checkpoint inhibitor, with corticosteroid management for immune-related adverse events as per standard practice, e.g., hold for grade 2 pneumonitis/colitis; discontinue permanently for grade 3 or higher. All dose modifications will be recorded prospectively.”Concomitant Medications: Supportive care will be provided to all patients according to clinical oncology guidelines. The use of other Chinese herbal decoctions with purported similar effects, anti-tumor Chinese herbal injections, Chinese patent medicines, thymic peptides, or other immunomodulatory biological agents is prohibited during the study period. Any changes in concomitant medications will be recorded.

### Outcome measures

2.7

#### Primary outcome

2.7.1

EFS: Defined as the time from randomization to the first occurrence of any of the following events: disease progression precluding curative surgery, local or distant recurrence, or death from any cause.

#### Secondary outcomes

2.7.2

Survival Outcomes:• DFS: Time from the date of surgery to tumor recurrence, metastasis, or death from any cause.• Overall Survival (OS): Time from randomization to death from any cause.• Cumulative 1-, 2-, and 3-Year Recurrence/Metastasis Rate: The proportion of patients experiencing recurrence or metastasis at 1, 2, and 3 years from randomization.• Cumulative 1-, 2-, and 3-Year Survival Rate: The proportion of patients alive at 1, 2, and 3 years from the date of surgery.Surgical Conversion Rate: Proportion of patients who successfully undergo R0 resection following neoadjuvant therapy.Infection and Complications:• Perioperative infection rate.• Incidence of early (≤30 days) and late (≤12 months) postoperative complications.Patient-Reported Outcomes:• QoL: Assessed using the Functional Assessment of Cancer Therapy - Gastric scale.• Symptom Burden: Assessed using the Edmonton Symptom Assessment System.• TCM Symptoms: Assessed using the MD Anderson Symptom Inventory - TCM Module.Treatment Delivery Indicators:• Chemotherapy Completion Rate: Proportion of planned adjuvant chemotherapy cycles completed.• Medication Adherence: Calculated based on the number of study drug packets consumed. Adherence will be categorized as <80%, 80-120%, and >120%. The number and percentage of patients in each category will be reported.Immunological Biomarkers: Levels of circulating T cells, regulatory T cells, CD4+ T cells, and CD8+ T cells.Serum Tumor Markers: Carcinoembryonic Antigen, Carbohydrate Antigen 72-4, Carbohydrate Antigen 19-9, and Carbohydrate Antigen 125.

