### Study design

2.1

This study is a multicenter, randomized, double-blind, placebo-controlled clinical trial conducted in China. It will be implemented across at least seven tertiary hospitals, including Hunan Cancer Hospital, Xiangya Hospital of Central South University, Guangdong Provincial Hospital of Traditional Chinese Medicine, Jiangsu Provincial Hospital of Traditional Chinese Medicine, the First Affiliated Hospital of Hunan University of Traditional Chinese Medicine, and Guangxi International Zhuang Medical Hospital. Central randomization with allocation concealment will be employed, stratified by the use of neoadjuvant chemotherapy ± immunotherapy. All participants will receive perioperative chemotherapy (SOX or XELOX) ± immunotherapy. In addition, patients in the experimental group will receive SQFWG, while those in the control group will receive a matched placebo containing 5% SQFWG. The study medication will be administered concurrently with chemotherapy and continued until disease progression, unacceptable toxicity, or completion of the perioperative treatment phase. All patients will be followed for 3 years. After completing the final treatment or upon reaching a study endpoint, patients will enter a follow-up phase with assessments scheduled every 3 months. The primary efficacy endpoint is event-free survival (EFS). **Figure 1** presents the flowchart for participant enrollment, intervention, and assessment. **Figure 2** illustrates the schedule of interventions and follow-up. The study phases are outlined in **Table 1**.

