#### Inclusion criteria

2.2.1

Histologically or cytologically confirmed adenocarcinoma of the stomach or gastroesophageal junction.Resectable or potentially resectable disease with a clinical stage of cT1-2bN1-3M0, cT3-4bN0M0, or cT3-4aN1-3M0 (Stage II–III).Previous anti-tumor treatment, including chemotherapy, radiotherapy, immunotherapy or targeted therapy, is not permitted;Adequate organ function, defined as:• Absolute neutrophil count ≥ 1.5 × 10^9^/L• Hemoglobin ≥ 9.0 g/dL• Platelet count ≥ 80 × 10^9^/L• Serum albumin ≥ 30 g/L• Serum total bilirubin ≤ 1.5 × upper limit of normal (ULN)• Aspartate aminotransferase and alanine aminotransferase ≤ 2.5 × ULN• Alkaline phosphatase ≤ 2.5 × ULN• Serum creatinine ≤ 1.5 × ULNKarnofsky Performance Status score ≥ 70.Age between 18 and 75 years.Willing and able to provide written informed consent.

*Potentially resectable disease is defined, as clinical stage II–III disease, according to CSCO gastric cancer guidelines and multidisciplinary team (including surgical oncologists and radiologists) assessment, including tumors considered technically unresectable at diagnosis but potentially convertible to R0 resection following neoadjuvant therapy.

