Multiple correction strategy: To control the type I error rate due to multiple secondary endpoints, we will apply a hierarchical testing procedure. The primary endpoint EFS will be tested first at α=0.05 (two-sided). Only if the primary endpoint is statistically significant will secondary efficacy endpoints (OS, DFS, 1-/2-/3-year recurrence/metastasis rates) be tested sequentially using a fixed-sequence procedure to preserve the overall α level. If the primary endpoint is not statistically significant, all secondary endpoints will be considered exploratory and reported descriptively without formal hypothesis testing. All other secondary endpoints (postoperative complications, symptom burden, TCM symptoms, immunological biomarkers, and serum tumor markers) will be reported descriptively with nominal *p*-values. These analyses are hypothesis-generating and will not be subject to formal multiplicity adjustment. Results will be interpreted with appropriate caution.

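### DFS and the 1-/2-/3-year survival rates are timed from surgery, an event that follows up to four cycles of randomized treatment, yet DFS is in the confirmatory test sequence

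*Protocol article*

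**What the plan says.** All references are to the protocol article.

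- Section 2.7.2 (Secondary outcomes) starts two measures at surgery. One is "DFS: Time from the date of surgery to tumor recurrence, metastasis, or death from any cause". The other is the cumulative survival rate: "The proportion of patients alive at 1, 2, and 3 years from the date of surgery".
- The same section starts OS elsewhere: "Overall Survival (OS): Time from randomization to death from any cause". The recurrence/metastasis rates also run from randomization. So does the primary endpoint, EFS (2.7.1): "Defined as the time from randomization to the first occurrence of any of the following events: disease progression precluding curative surgery".
- Treatment precedes surgery. Section 2.6: "The preoperative phase will consist of 2–4 cycles of neoadjuvant SOX or XELOX chemotherapy, with or without immunotherapy". Section 2.1: "The study medication will be administered concurrently with chemotherapy and continued until disease progression, unacceptable toxicity, or completion of the perioperative treatment phase".
- Surgery is not assured. Section 2.2.1 admits "tumors considered technically unresectable at diagnosis but potentially convertible to R0 resection following neoadjuvant therapy", and 2.7.2 lists the R0 resection rate after neoadjuvant therapy as a secondary outcome.
- Section 2.9 says efficacy is analysed on a Full Analysis Set following intention to treat, and on a Per-Protocol Set. If EFS is significant, it has "secondary efficacy endpoints (OS, DFS, 1-/2-/3-year recurrence/metastasis rates) be tested sequentially using a fixed-sequence procedure to preserve the overall α level".

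**The concern.** Timing DFS from surgery is natural when patients are randomized after surgery. Here they are randomized before neoadjuvant treatment, so having an operation is a consequence of what happened on study drug. Patients who progress, die or stay unresectable before surgery have no DFS time at all. Those who remain in each arm are no longer groups formed by randomization.

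If SQFWG brings more marginal tumours to surgery, its operated group gains patients with a poor prognosis, and DFS looks worse than it should. If it brings fewer to surgery, DFS looks better. Controlling the type I error across the sequence does not repair a comparison of non-randomized groups. In the listed order, a DFS test that fails for this reason would also stop the recurrence/metastasis tests behind it, and those are closest to the trial's stated aim.

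The survival rates have the same selection. In addition, three-year survival as defined and OS at three years would be different quantities in different populations.

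**Working it through.** **1. Definitions side by side**

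| Measure | Clock starts | Defined for unoperated patients | In the test sequence |
|---|---|---|---|
| EFS (primary) | randomization | yes; progression precluding curative surgery is an event | first |
| OS | randomization | yes | listed second |
| DFS | surgery | no | listed third |
| Recurrence/metastasis rates | randomization | no rule stated | listed fourth |
| 1-/2-/3-year survival rates | surgery | no | no |

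A measure with no start time for some randomized patients cannot be analysed in all of them. The article gives no rule for these patients and no other origin for DFS, so 2.7.2 and 2.9 conflict.

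**2. How many patients DFS would rest on**

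The article gives no share reaching surgery. Of 286 randomized, assumed shares of 95%, 90%, 80% and 70% leave 286 × 0.95 = 272, 257, 229 and 200.

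**3. Size of the selection effect, with no postoperative drug effect**

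Assumptions:
- A share r_C of controls and a larger share r_T of the SQFWG arm reach surgery.
- The extra operated patients have k times the hazard of the others.
- Follow-up ends at 36 months.
- The base hazard is λ = −ln(0.44)/36 = 0.0228 per month. This borrows the 44% control 3-year EFS from section 2.5 as a stand-in, because no postoperative rate is given.

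The extra patients make up f = (r_T − r_C)/r_T of the operated SQFWG group. Its DFS curve is (1 − f)·exp(−λt) + f·exp(−kλt), against exp(−λt) in controls.

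Example with 80% versus 90% and k = 3: f = 0.10/0.90 = 0.111. At 36 months, SQFWG DFS is 0.889 × 0.44 + 0.111 × 0.44³ = 0.391 + 0.009 = 0.401, against 0.440.

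Large-sample Cox hazard ratios, SQFWG versus control:

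| Operated, control vs SQFWG | k = 2 | k = 3 | k = 4 |
|---|---|---|---|
| 80% vs 85% | 1.04 | 1.07 | 1.08 |
| 80% vs 90% | 1.08 | 1.13 | 1.15 |
| 75% vs 85% | 1.09 | 1.13 | 1.16 |
| 75% vs 90% | 1.12 | 1.20 | 1.23 |

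If the control arm has the higher surgery rate instead, the ratios invert: 1/1.04 = 0.96 to 1/1.23 = 0.81, an apparent benefit. The stand-in hazard matters modestly: with 55% in place of 44%, the range is 1.05–1.27.

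**4. Effect on the test at the planned size**

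A second simulation used 143 per arm, prognosis as a continuous factor that affects both reaching surgery and DFS, and again no drug effect on any patient's DFS. Two-sided rejection at 0.05 was about 5% (HR 1.00) with 85% operated in both arms. It was 6–9% (HR 1.06–1.09) at 80% versus 90%, and 7–12% (HR 1.08–1.14) at 75% versus 90%.

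**The case against.** The strongest reply is that little hangs on DFS. It is tested only after EFS and, in the listed order, OS have succeeded, and both of those start at randomization. A DFS claim could add to a positive result but not create one, and the block on the recurrence tests could matter only after those two successes. That stands and limits the severity.

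It is also fair that the R0 resection rate will be reported, so a reader could see an imbalance, and that the exact DFS population may be set out in a document not shown. But the time origin and the place in the sequence are fixed in this article, and reporting resection rates beside DFS does not make the operated groups comparable.

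A reader might infer more than the documents support:

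- That operated patients receive a guaranteed event-free period. They do not. The clock starts at surgery, so earlier time is dropped, not credited. The defect is selection.
- That the survival rates are part of the confirmatory claim. They are not in the listed sequence.
- That the plan favours SQFWG. The direction depends on which arm has more surgery. In the scenarios tabulated, where SQFWG has more, the bias runs against it.

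**Conclusion.** The point holds in a limited form. DFS and the survival rates compare subsets selected after randomization, cannot meet the stated intention-to-treat analysis, and, for the survival rates, do not share an origin with OS. A formal test of DFS so defined is not a randomized comparison. The primary conclusion and OS are untouched, so this should be corrected but does not threaten the trial's main result.

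The size is not known from the article. Roughly 1.04–1.2 for the DFS hazard ratio (1.23 at the most extreme combination) rests on assumed resection rates, assumed 2- to 4-fold hazards and a borrowed base hazard. If surgery rates and selection are the same in both arms, the simulation shows no distortion.

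**What to change.** 1. Take DFS out of the fixed sequence in 2.9 and call it supportive in operated patients, with numbers and reasons for non-surgery by arm. Do not narrow it to R0-resected patients, which would condition on a further post-randomization outcome. To keep it confirmatory instead, time it from randomization or a common landmark in all randomized patients, with failure to reach surgery counted as an event. Timed that way, it comes close to EFS.
2. Define the 1-/2-/3-year survival rates as Kaplan-Meier estimates of OS at 12, 24 and 36 months from randomization.
3. If the recurrence/metastasis rates then follow OS, analyse them in all randomized patients, with death without recurrence as a competing event and progression precluding surgery counted as an event. Otherwise an arm with fewer resections or more early deaths could look better on recurrence.

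The cost is wording in 2.7.2 and 2.9, with no new data beyond recording why surgery did not take place. The downside of the first option is one fewer confirmatory secondary endpoint. Section 3 reports 61 participants recruited and no analysis performed, so the change can still be made before any results are seen.

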### Sample size calculation

2.5

This is a randomized, placebo-controlled superiority trial with a 1:1 allocation ratio. The primary endpoint is EFS. Based on the KEYNOTE-585 trial results (11), the assumed 3-year EFS rate for the control group (receiving perioperative chemotherapy ± immunotherapy) is 44%. We hypothesize that the addition of SQFWG will increase the 3-year EFS rate by 20% (absolute improvement), resulting in a rate of 64% for the experimental group. Using a two-sided significance level (α) of 0.05 and a power (1-β) of 80%, and assuming a constant accrual rate over an enrollment period of 36 months, the sample size was calculated using PASS software (version 15). This calculation yielded 114 participants per group. To account for an estimated 20% dropout rate, the final target enrollment is set at 143 participants per group. The design is event-driven, requiring a sample size of 286 cases. The duration of enrollment is 3 years, and the total study duration is 5 years, taking into account a 20% dropout rate.

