### Statistical analysis

2.9

All analyses will be performed using SAS software (version 9.4). Efficacy analyses will be conducted on both the Full Analysis Set (intention-to-treat principle) and the Per-Protocol Set. Safety analyses will be performed on the Safety Set. Prespecified subgroup analyses based on randomization stratification factors, and multivariable adjustment will be used to minimize the influence of treatment heterogeneity. Time-to-event endpoints (EFS, DFS, OS) will be summarized using Kaplan-Meier survival curves and compared between groups using the log-rank test. The Cox proportional hazards model will be employed for multivariate analysis to adjust for potential confounding variables. All statistical tests will be two-sided, with a *p*-value < 0.05 considered statistically significant.

Subgroup analyses: To explore potential beneficiary characteristics, we will perform prespecified subgroup analyses according to baseline clinical factors (age, sex, tumor clinical stage, T stage, N stage, PD-L1 CPS, MSI/MMR status, chemotherapy regimen, immunotherapy use, baseline Karnofsky score, TCM syndrome classification, and relevant biomarker subgroups). For each subgroup, the treatment effect on EFS will be estimated, and interactions between treatment and subgroup factors will be tested using the Cox model. The model selection strategy will be forced entry of these pre-specified variables (no stepwise selection) to avoid overfitting and multiplicity issues. Proportional hazards assumption will be tested using Schoenfeld residuals. These analyses are exploratory and hypothesis-generating; no adjustment for multiple testing will be applied. This study is not powered for formal predictive model development or validation.

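### The 1-/2-/3-year recurrence/metastasis rates are formally tested but defined as plain proportions with no allowance for censoring, which biases the 3-year figure in each arm

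*Protocol article*

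**What the plan says.** Section 2.7.2 (Secondary outcomes) defines the cumulative 1-, 2- and 3-year recurrence/metastasis rate as "The proportion of patients experiencing recurrence or metastasis at 1, 2, and 3 years from randomization". It names no denominator. It gives no rule for patients who are lost, who have not reached the landmark at the cut-off, or who die without recurrence.

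Section 2.9 (Statistical analysis) assigns methods that handle censoring to a closed list: "Time-to-event endpoints (EFS, DFS, OS) will be summarized using Kaplan-Meier survival curves and compared between groups using the log-rank test". The recurrence/metastasis rates are not on it. The multiplicity paragraph of the same section gives them a formal test: if EFS is significant, "secondary efficacy endpoints (OS, DFS, 1-/2-/3-year recurrence/metastasis rates) be tested sequentially using a fixed-sequence procedure".

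Four statements bear on how many patients will have a known 3-year status:

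- Section 2.5 (Sample size calculation) expects 20% dropout, with 3 years of enrollment in a 5-year study.
- Section 3 (Trial status and progress) has recruitment from 1 November 2025 to 30 August 2028 and the primary analysis in December 2030.
- Section 2.1 (Study design) says that all patients are followed for 3 years.
- Section 2.2.5 keeps up 3-monthly survival contact after discontinuation or withdrawal.

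**The concern.** A simple proportion at 36 months is well defined only if every patient's status at 36 months is known. Otherwise someone has to choose a denominator. Keeping patients with unknown status in the denominator as recurrence-free pulls the rate down. Dropping them pushes it up, because an early recurrence makes a patient's status known whereas a patient without recurrence must be observed for the full 36 months to count.

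Reducing postoperative recurrence and metastasis is the stated aim of the trial, so this is the figure many readers will look for. As defined, the published 3-year rate in each arm would reflect dropout, follow-up length and the chosen denominator as well as recurrence. It would not be comparable with rates from other trials.

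**Working it through.** **Plan's own figures.** The article gives no planning figure for this endpoint. Its dropout allowance reproduces: 114 / 0.8 = 142.5, rounded up to 143 per group.

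**Inputs from the article.** 3-year EFS is 44% (control) and 64% (SQFWG), and dropout is 20% (Section 2.5). Timing comes from Sections 2.5, 3 and 2.1.

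**Assumptions.** Events are exponential and, in the main calculation, all are recurrences. Loss is exponential, reaches 20% by 36 months and is equal in both arms. Accrual is uniform.

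**Step 1. Patients who cannot reach 36 months by the cut-off.**
- Section 2.5 timing: potential follow-up 24-60 months, so (36 − 24)/36 = 33%, about 95 of 286.
- Section 3 timing: 34 months of accrual and about 28 months after the last entry, so potential follow-up is 28-62 months and (36 − 28)/34 = 24%, about 67 of 286.
- Section 2.1 reading: none.

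**Step 2. Hazards per month.**
- Control: −ln(0.44)/36 = 0.0228
- SQFWG: −ln(0.64)/36 = 0.0124
- Loss: g = −ln(0.8)/36 = 0.0062

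**Step 3. Observed quantities.** Let C(t) be the probability that a patient's potential follow-up is at least t, and h the event hazard.
- Observed recurrence by 36 months: R = ∫ h·exp(−(h+g)t)·C(t) dt from 0 to 36
- Observed recurrence-free at 36 months: N = exp(−36(h+g))·C(36)
- Proportion over all randomized = R; proportion over known status = R/(R+N)

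**Step 4. Example with everyone followed for 36 months (C = 1), control.**
- R = 0.0228/(0.0228+0.0062) × (1 − 0.44×0.8) = 0.786 × 0.648 = 0.510
- N = 0.44×0.8 = 0.352
- R/(R+N) = 0.510/0.862 = 0.591

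**Step 5. Results at 3 years** (true values 56% control, 36% SQFWG, difference 20 points).

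| Potential follow-up | All randomized: control / SQFWG (difference) | Known status: control / SQFWG (difference) |
|---|---|---|
| 28-62 months (Section 3) | 50.1% / 31.9% (18.2) | 65.1% / 44.9% (20.2) |
| 24-60 months (Section 2.5) | 49.1% / 31.2% (18.0) | 67.7% / 47.7% (20.0) |
| 36 months for all (Section 2.1) | 51.0% / 32.5% (18.4) | 59.1% / 38.9% (20.3) |

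**Step 6. Earlier landmarks.** Every timeline gives at least 24 months of potential follow-up, so only dropout matters. Step 4's formula with 24 in place of 36 gives, for control, 39.4% or 44.2% against a true 42.2%, and for SQFWG 24.0% or 27.3% against 25.7%. At 12 months the control figures are 23.1% or 24.7% against 23.9%.

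**Step 7. Deaths without recurrence.** Suppose a share q of events are such deaths (q is not in the article). If these patients stay in the denominator, every 3-year figure in Step 5, true or observed, is multiplied by 1 − q. With q = 20% and Section 3 timing, the control cumulative incidence is 0.8 × 56% = 44.8%, against 40.1% over all randomized and 52.1% over known status. Removing those deaths from the known-status denominator as well gives 59.8%. For q of 10-30% the control cumulative incidence is 50.4-39.2%.

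**Step 8. Type I error.** This was simulated with 143 per arm, 24-60 months of follow-up, q = 20% and the control hazard in both arms. With 20% dropout in each arm, rejection was 4.8% (all randomized) and 5.0% (known status). With an assumed split of 10% versus 30%, it was about 10% and 6.6%.

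**The case against.** The best defense is that the article names no estimator. The endpoint is labeled cumulative and grouped with the survival outcomes, and the neighboring survival rate is worded the same way although it would usually be read from a Kaplan-Meier curve. The denominator could be left to an analysis plan that is not shown. This has some force: the article does not state that censoring will be ignored. But it does more than stay silent. It defines the endpoint as a proportion and lists the endpoints that receive survival methods, without this one.

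A second defense is that Section 2.1 promises 3 years of follow-up for all and Section 2.2.5 continues contact after withdrawal. This narrows the bias but does not remove it: with 20% loss the control figure is still 51% or 59% rather than 56%. Treating the whole 20% as loss of status is an assumption, and better tracing would shrink the effect.

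A reader might also infer four stronger points that the documents do not support:

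- **That the comparison between arms is compromised.** The difference stays at 18-20 points under either denominator, and equal dropout leaves the type I error at about 5%. Inflation needs unequal dropout, which the article does not predict.
- **That all three landmarks are equally affected.** The 1- and 2-year rates face dropout only.
- **That counting deaths without recurrence as non-recurrent is a flaw peculiar to the proportion.** A competing-risks cumulative incidence has the same property. With complete follow-up and all randomized patients in the denominator, the two are identical.
- **That the trial's main conclusion is at risk.** The rates are listed after OS and DFS, and EFS already captures recurrence with suitable methods, counting "disease progression precluding curative surgery, local or distant recurrence, or death from any cause".

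**Conclusion.** The point holds for the 3-year rate as an estimate in each arm. Under the article's own dropout and timing, a true 56% in the control arm would be reported as about 49-51% or 59-68% depending on the denominator. A true 36% in the SQFWG arm would be reported as about 31-33% or 39-48%. These ranges rest on exponential events that are all recurrences and on 20% exponential loss by 36 months, equal between arms. The between-arm difference moves by about 2 points at most.

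The definition should be corrected because the endpoint is formally tested and addresses the trial's stated aim. It is not a threat to the primary analysis.

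**What to change.** Redefine the rates in Section 2.7.2 as the cumulative incidence of recurrence or metastasis from randomization in all randomized patients, estimated by Aalen-Johansen. Censor at the last disease assessment or the data cut-off, and treat death without recurrence as a competing event. Report the 12-, 24- and 36-month estimates by arm with confidence intervals.

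In Section 2.9, add the endpoint to those analyzed with time-to-event methods and base the between-arm test on these estimates. Comparisons at the fixed times would do. A Gray test stratified by the randomization factor is one option, but replacing the three landmark tests by one is not required. State that the result is read alongside EFS and OS, because deaths without recurrence lower the recurrence incidence. The estimator still assumes non-informative censoring, so losses should be reported by arm.

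The cost is a change of wording and a standard SAS procedure, with no new data. Section 3 reports that no analysis has been performed, so the change can be made now without any suspicion that results drove it. The follow-up statements in Sections 2.1, 2.5 and 3 should be reconciled at the same time.
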